**13-5. Process of Withdrawal**

(1) Dropout cases must be appropriately managed and treated, and the development must be observed and recorded. The reason of withdrawal must be recorded in the CRF.

(2) All the test results up to the time of withdrawal, the date, reasons, treatments and progress at the time of withdrawal must be recorded in the CRF.

(3) If subjects do not show up for a visit, mail, interview, and phone calls can be used to investigate the reasons and progress, and the results are recorded in the CRF.

(4) The dropout subjects are not replaced with new subjects.

(5) If subjects withdraw in the middle of the clinical trial, they are not required to explain the reason, but investigators must try to confirm the reason upon considering the subject rights.

(6) If there is an outcome of efficacy and safety evaluation (such as AE and concomitant medication) at the time of withdrawal, it must be included in the analysis unless this distorts the validity of the clinical trial.

(7) The result of pregnant subject can be collected only for ethical purpose and the observation on that subject will be continued even after the drop-out.

**13-6 Protocol Violation**

If a violation of protocol is confirmed, investigators must inform the investigator must decide continuation or discontinuation of the clinical trial. The details and reasons of the protocol violation must be recorded in the CRF. Continuation or discontinuation of the clinical trial is determined by the investigators considering the effects of the violation on the efficacy and safety of the investigational device.

**14. Assessment of Efficacy Criteria**

**14-1. Assessment of Efficacy Criteria [6], [8], [9], [12], [13], [17], [23], [24], [25], [26], [27]**

The preoperative and postoperative physical function will be measured.

- Shoulder range of motion (Abduction, Horizontal abduction, Flexion, External rotation)

- Evaluation on the upper limbs’ locomotive capacity

- The evaluation on pain derived from the movement

**14-2. Assessment of Safety Criteria**

Whether the adverse events occur or not and the abnormal findings on laboratory test

**14-3. Assessment of Other Criteria**

The postoperative drainage volume, postoperative therapy (cancer chemotherapy, anti-hormone therapy, target therapy, radiotherapy)

**15. Evaluation Methods and Interpretation Methods**

**15-1 Assessment of Efficacy Methods and Interpretation**

(1) Evaluate using the questionnaire prepared by the researcher and subject

(2) Primary Efficacy Criteria Analysis

The each range of motion’s angle is measured at 4 states of ROM (range of motion) using the universal full-circle manual goniometer on the preoperative day and the 3th month, the 6th month, and the 12th month following the surgery. The measured value is used to analyze the significance at each ROM’s state comparatively by performing the one side and two sample student T-test with the difference and the variance between two groups measured at each period (from preoperative day to the 3th month, the 6th month, and the 12th month following the surgery). When there is over 10 degree differences between two groups (that is the lowest value of confidential interval is over 10), the investigational group is superior to the control. (The over 10 degrees difference of two group is considered to be significant clinically when comparing it).

(3) Secondary Efficacy Criteria Analysis

- Evaluation on the upper limbs’ locomotive capacity (questionnaire – DASH (disability of the arm, shoulder and hand))

The score of DASH questionnaire consist of 30 questions is calculated based on the items filled by the subject.

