**H_0_ : D ≤ 10 H_1_ : D〉10 (D=Experimental group(EG) ROM Mean – Control group(CG) ROM Mean)**

* Basis of Calculation: Assumptions for estimating the effective subject number.

① Significance level α = 0.025

② The EG estimation number is 1 time that of CG.

③ Type 2 error (β) is 0.1, and statistical power 90% is maintained.

④ The difference in the average value between two groups: 10 degree.

[figure not shown]

[figure not shown]

[figure not shown]

| Power | N1/N2 | Equivalence Margin  (E) | Actual  Difference  (D) | Significance  Level  (Alpha) | Beta | Standard  Deviation1  (SD1) | Standard  Deviation2  (SD2) |
| --- | --- | --- | --- | --- | --- | --- | --- |
| 0.90022 | 23/23 | 5 | 10 | 0.025 | 0.09978 | 5 | 5 |
| 0.80044 | 17/17 | 5 | 10 | 0.025 | 0.19956 | 5 | 5 |
| 0.90004 | 86/86 | 5 | 10 | 0.025 | 0.09996 | 10 | 10 |
| 0.80003 | 64/64 | 5 | 10 | 0.025 | 0.19997 | 10 | 10 |
| 0.90022 | 191/191 | 5 | 10 | 0.025 | 0.09978 | 15 | 15 |
| 0.80044 | 143/143 | 5 | 10 | 0.025 | 0.19956 | 15 | 15 |
| 0.91250 | 23/23 | 10 | 15 | 0.025 | 0.08750 | 5 | 5 |
| 0.80704 | 17/17 | 10 | 15 | 0.025 | 0.19296 | 5 | 5 |
| 0.90323 | 86/86 | 10 | 15 | 0.025 | 0.09677 | 10 | 10 |
| 0.80146 | 64/64 | 10 | 15 | 0.025 | 0.19854 | 10 | 10 |
| 0.90022 | 191/191 | 10 | 15 | 0.025 | 0.09978 | 15 | 15 |
| 0.80044 | 143/143 | 10 | 15 | 0.025 | 0.19956 | 15 | 15 |

Suppose that the 10% subject is dropped out in the middle of trial, the necessary total subject is 192 persons composing of 96 persons for the experimental group and 96 persons for the control.

| Target subject number | EG | CG | In total subject number |
| --- | --- | --- | --- |
| Subject number for final efficacy evaluation | 86 | 86 | 172 |
| Subject number in consideration of drop-out rate (10%) | 96 | 96 | 192 |

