**<External rotation>**

The movement of external rotation is measured with his/her shoulders abducted at 90° degrees, elbows flexed at 90° degree, forearms pronated in the lying and standing position. When measuring in standing position, the patient’s forearms shall be placed to the floor horizontally and his/her palms shall be directed toward the floor.

[figure not shown]

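### The primary analysis makes at least 12 one-sided comparisons under one superiority rule, without saying which must meet it or how many, while the sample size covers one.

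*Protocol*

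**What the plan says.** - **Endpoints.** Section 14-1 lists four motions: "Shoulder range of motion (Abduction, Horizontal abduction, Flexion, External rotation". Section 15-1 (2) makes all four primary: each angle "is measured at 4 states of ROM (range of motion) using the universal full-circle manual goniometer on the preoperative day and the 3th month", and again at 6 and 12 months.
- **Time points.** Changes are taken "from preoperative day to the 3th month, the 6th month, and the 12th month following the surgery".
- **Test.** Significance is assessed for each motion "by performing the one side and two sample student T-test with the difference and the variance between two groups measured at each period".
- **Success rule.** The device is superior "When there is over 10 degree differences between two groups (that is the lowest value of confidential interval is over 10". No motion, position, visit or required number of wins is attached to this.
- **Measuring positions.** Section 11-2 takes external rotation with "forearms pronated in the lying and standing position". Under shoulder flexion, it also refers to the coronal, scapular and sagittal planes for abduction and flexion.
- **Sample size.** Section 8-3 states a single difference D in an unspecified mean range of motion (null: D at most 10; alternative: D above 10), with "Significance level α = 0.025". It gives 86 evaluable patients per arm, raised to 96 for 10% dropout.

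Nowhere does the protocol name a lead motion or visit, a composite, or an order of testing.

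**The concern.** The hypothesis, the alpha and the sample size describe one comparison, but the primary analysis describes at least 12. The success rule does not connect the two. The plan therefore does not define what result would make the trial positive, and the deciding motion, visit or number of wins could be chosen after the data are seen.

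The two obvious ways to fill the gap have different consequences. If one win out of 12 is enough, the trial-wise false-positive rate near the 10-degree boundary exceeds the stated 2.5%. If all 12 must win, the planned power no longer applies.

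**Working it through.** **Inputs from the protocol.** Four motions (14-1); three follow-up visits (15-1 (2)); one-sided alpha 0.025, SD 10, power 90%, 86 per arm (8-3); lower limit above 10 degrees (15-1 (2)). The protocol gives no correlations between motions or visits, so those below are assumptions.

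**Step 1: reproduce the plan's figure.** Take one comparison, one-sided alpha 0.025, SD 10, and a gap of 5 degrees between true difference and margin, as in the 8-3 table rows for 86 per arm with SD 10.
- Normal approximation: n = 2 × 10² × (1.960 + 1.282)² / 5² ≈ 84.1, so 85 per arm.
- Noncentral t: power is 0.8999 at 85 and 0.9032 at 86, so 86 per arm.
- Dropout: 86 / 0.9 = 95.6, so 96 per arm.

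The figure is reproduced, and it is for one comparison.

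**Step 2: count the tests.** 4 × 3 = 12. The count rises if the two external rotation positions, or the planes, are analysed separately.

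**Step 3: any one win suffices, all true differences at D = 10.** With independent tests, 1 − 0.975¹² = 0.262. With correlated tests (multivariate normal simulation of the 12 statistics, 1,000,000 draws):

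| Correlation between motions / visits | Chance of at least one false claim |
|---|---|
| 0.3 / 0.3 | 22.1% |
| 0.5 / 0.5 | 18.1% |
| 0.7 / 0.7 | 13.3% |
| 0.9 / 0.9 | 7.5% |

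**Step 4: below the boundary.** The standard error of the difference is 10 × √(2/86) = 1.525. A lower limit above 10 needs an observed difference above about 10 + 1.96 × 1.525 = 13.0 degrees. For a true difference D the per-test chance is p = 1 − Φ(1.96 + (10 − D)/1.525), and the chance over 12 independent tests is 1 − (1 − p)¹².
- D = 9: p = 0.0045, giving about 5%.
- D = 8: p = 0.0005, giving about 0.6%.
- D = 0: essentially 0.

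**Step 5: all 12 must win.** Type I error stays at or below 0.025, because every test has to pass. Joint power at 90% per comparison is 0.9¹² = 0.282 if independent. By simulation it is about 57% at correlations 0.5 / 0.7, 66% at 0.7 / 0.8 and 77% at 0.9 / 0.9.

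**Step 6: cost of splitting alpha.** The first Holm step uses 0.025 / 12 = 0.00208. With 86 per arm, per-comparison power falls from 0.90 to about 0.65. Restoring 90% at that level needs about 140 per arm, or 140 / 0.9 = 155.6, so 156 enrolled per arm against the planned 96.

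**The case against.** Four points can be made for the plan.

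1. **The text does not say that any one win is enough.** A reader might infer this from the testing at each motion and each visit. Section 15-1 (2) states neither an any rule nor an all rule, and its wording also fits separate claims for each motion. This stands: the defect is an undefined primary comparison, and 26% is the result of one reading.

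2. **An ineffective device is hardly at risk of being declared superior.** A reader might take 26% as the chance of approving a device with no effect. Under the written lower-limit rule that is wrong, as step 4 shows. The inflation concerns devices within a degree or two of the 10-degree threshold. It would reach the no-effect case only if the significance testing in 15-1 (2) meant separate tests against zero that could themselves support a claim. The section names no such null value, and its superiority rule is the limit above 10. What remains is that, on the any reading, the error rate over the protocol's own null (D at most 10) exceeds 2.5%.

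3. **Requiring all 12 does not break type I control.** This is correct. Only power is lost on that reading.

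4. **A statistical analysis plan may hold the multiplicity method.** It may, so the lack of a named adjustment is not by itself a fault here. The primary endpoint and the success rule are different. The protocol sets them in 8-3 and 15-1 (2), and the two sections do not fit together.

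The joint-power figures also take 90% per comparison on trust. Section 15-3 gives 80%, and 8-3 states a 10-degree difference alongside a 10-degree null boundary. Those are separate matters, and neither would raise joint power.

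**Conclusion.** The point holds as a gap in the definition of the primary comparison and its success rule. Sections 8-3 and 15-1 (2) cannot both be followed with the stated error rates until one comparison, or an explicit win rule, is named.

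If any win counts, the false-claim rate at D = 10 for all comparisons is 26% under independence and about 8% to 22% at assumed correlations of 0.9 down to 0.3, against 2.5% stated. It drops quickly for smaller true differences. If all must win, joint power is about 28% to 77% instead of 90%. These sizes rest on the assumed correlations, a common true difference across the 12 comparisons, and 86 evaluable patients per arm with SD 10. At none of the correlations examined are both the stated alpha and the stated power recovered.

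The documents do not support a claim that the trial has a 26% chance of endorsing an ineffective device.

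**What to change.** In 8-3 and 15-1 (2), before unblinding, name one primary comparison: one motion, in one measuring position or plane, at one visit. The choice is the sponsor's. That comparison alone carries the one-sided 0.025 rule of a lower limit above 10 degrees, and D in 8-3 is defined as that quantity. The other comparisons become secondary, tested in a written fixed order only after the primary succeeds.

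This costs wording in the protocol, and in the statistical analysis plan if there is one. No alpha is split, so multiplicity does not require a larger sample. The downside is that a single favourable motion or visit no longer earns a superiority claim by itself.

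If the sponsor will not choose, Holm across all 12 is a fallback, with its cost written down: about 0.65 power per comparison at the first step with 86 per arm. The chance of at least one win stays higher than that, but the planned 90% for a given comparison does not. The confidence limits compared with 10 degrees must then be set at the matching adjusted level.

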**6-2. Background**

The various adverse events on the upper limbs such as the pain on the arm, the muscle weakness, the lymphedema, hypofunction of shoulder joint, and etc. occur following the breast cancer surgery. The shrinkage in the range of shoulder joint’s motion and the muscle weakness lead to the reduction in activities’ scope of daily living and the decline the quality of life [2-6]. Therefore, the treatment and effort to prevent the complication which occurs especially when the axillary lymph node dissection is performed is needed. Koostra et al. reported the complication (such as lymphedema, the range of shoulder joint’s motion, muscular strength, the exercise of upper limbs, and etc.) occurrence rate of patients who underwent the surgery on the sentinel node is lower than it of patients who underwent the axillary lymph node dissection in terms of statistical significance found at prospective studies. The significant factor related to the reduction in the range of shoulder joint’s motion affects the treatment method and the recovery period [1].

The occurrence rate of pectoralis tightness and the reducing degree in the range of shoulder joint’s motion of patients who underwent the mastectomy are higher than those of patients who underwent the breast preservation surgery. The quality of radiotherapy subsequent to the surgery also affects the occurrence rate of above-mentioned complications. The reducing degree on the range of shoulder joint’s motion is the largest within 12 months subsequent to the surgery and its reducing degree is small since that time [3-6].

Since the adhesion of surgical site which can occurs after the total mastectomy causes the reduction in the range of shoulder joint’s motion and the pain, the measure for reducing the above-mentioned symptoms significantly is needed by developing the method to prevent the adhesion. The fact that the application of HA-CMC onto the surface of pectoral muscle and serratus anterior muscle, the treatment for preventing the adhesion followed by the surgery, widened the range of shoulder joint’s motion of breast cancer patients and reduce their pain is discovered in the previous study on HA-CMC [17]. In addition, the other studies on HA-CMC showed the range of joint’s motion is widened after the application of HA-CMC which lessened the adhesion degree [21].

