**10.3 Methods of Clinical Trial**

(1) Clinical Trial Design

The eligibility evaluation is conducted with the subject who underwent the modified radical mastectomy or breast preservation surgery and the axillary lymph node dissection at Asan medical center and signed at the consent form voluntarily subsequent to the screening test. The subject who isn’t included in the exclusion criteria visits the hospital on the operation day and undergoes the modified radical mastectomy or breast preservation surgery and the axillary lymph node dissection. Then, the subject is assigned to the investigational group or control according to the random assignment slip.

 EG: Guardix SG

 CG: Not applicable

That means the investigational device will be or won’t be applied onto the surgical site of subject depending on her group. Since the investigational device is applied inside of subject in the middle of surgery under anesthetic, the subject is unaware of treatment’s detail.

The related tests will be performed on the 7th, 3, 6 and 12 months subsequent to the surgery. In addition, the double-blind policy is maintained since the application of investigational device is performed by the expert who has a medical expertise and technique on the surgery and the application of investigational device, and the evaluator couldn’t know about the rule of random assignment and the allocation of subject to the group since the evaluator isn’t involved to the application of investigational device.

(2) Random Assignment of Subjects

In this clinical trial, random assignment was used to reduce bias that could be involved in the assignment of EG and CG, and to enhance the effects of comparison. To compare the precise difference in the range of motion of patient who underwent the partial mastectomy or total mastectomy, the subjects are assigned to each group randomly in similar proportion.

Our random assignment method is the block random assignment performed after generating random numbers (upto 4 places of decimals) for each subject using Excel’s random function (RAND). The sealed assignment slip is distributed to the subject. The sponsor of clinical trial provides the blinded slip which the investigational group or control is written down according to the randomly assigned subject table.

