**11. Monitoring Items and Monitoring Methods**

**11-1 Monitoring Items and Methods**

(1) Information Consent and Demographical Data

Before participating in the clinical trial, the purpose and procedure of clinical trial are explained to subject in detail and demographical information such as the receipt of the written consent and date, subjects’ initials, height, and BMI is recorded in the CRF. The copy of informed consent form is provided to the subject after receiving the written consent from subject.

(2) Past History and Physical function

The subject will be informed about the clinical trial continually. We recorded the stage of disease, medical history, the info related to the predisposing conditions on the shoulder joint, blood test, the range of shoulder joint’s motion, the evaluation on the exercise capability of upper limbs, and the evaluation on pain derived from the movement.

(3) Subject Eligibility Evaluation (Inclusion/Exclusion Criteria checking)

recorded the result conducted after evaluating whether the suitable subject is selected according to the inclusion/exclusion criteria based on the consent for the participation of clinical trial, demographical survey, medical history, the preoperative histological diagnosis, and etc.

(4) Observation items related to the surgery

- Basic information on the surgery

Operation date, Name of surgery, histopathological diagnosis, TNM stage, postoperative therapy (cancer chemotherapy, anti-hormone therapy, target therapy, radiotherapy)

- Safety evaluation

Adverse events (complication discovered during the hospitalization and surgery-related complication), Measurement of drainage volume subsequent to surgery, Observation of infectious symptom, Complete blood count exam (POD#7)

(5) Physical function (Before surgery, after surgery 3, 6, 12 months)

- Efficacy evaluation

Shoulder range of motion (Abduction, Horizontal abduction, Flexion, External rotation), Evaluation on the upper limbs’ locomotive capacity, the evaluation on pain derived from the movement, Evaluation on the lymphedema using the analysis of body composition

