**15-3 Statistical Analysis**

(1) Methods: One side, Two sample student t-test, Chi-square test, Fisher’s exact test

(2) Main analysis: ITT analysis

(3) Additional analysis: PP analysis

(4) Statistical power: 80%

* When performing the statistics for effectiveness evaluation, the information of subject who stopped to participate in or was dropped out from clinical trial is excluded from the compliance group (per protocol group) and is dealt as a missing value when the subject is assigned to the analysis group according to assignment table.

(5) General Principals of statistical analyses

The subject data of this study were analyzed through ITT (Intention to Treat) analysis and PP (Per Protocol) analysis.

In the ITT analysis, all the data obtained from the subjects who used the investigational device at least once after they were randomly assigned to the group were used. The above-mentioned subject’s information is excluded from the analysis for primary and secondary the missing value at the primary and secondary is discovered.

In the PP analysis, ITT analysis was data obtained from the subjects who completed the clinical trial according to the protocol were included. And the above-mentioned subject’s safety endpoint shall be included in ITT group. The value of subject which is out of clinical trial’s policy critically and may affect the efficacy evaluation (Exclusion criteria 2. The subject who is diagnosed as a breast cancer, absent on visit 1 and 2(each), assigned to the incorrect group, and experiences the severe adverse events during the clinical trial) will be included in the ITT group analysis with being excluded from the PP group analysis.

The efficacy evaluation was conducted using The efficacy evaluation was conducted using the ITT and PP analysis as a main method, while the PP analysis was used as an auxiliary method when the analysis results were inconsistent. The results of both analyses were compared. Demographical evaluation and safety evaluation were basically analyzed through the ITT analysis.

(6) Demographical Data

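### The primary test is an unadjusted t-test on change; adjusting for baseline and surgery type would cost nothing and would usually, though not always, gain precision

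*Protocol*

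**What the plan says.** Section 15-1 (2) analyses each of the four shoulder motions by "performing the one side and two sample student T-test with the difference and the variance between two groups measured at each period", where the periods run "from preoperative day to the 3th month, the 6th month, and the 12th month following the surgery". The experimental arm is called superior when the lower confidence limit for the difference exceeds 10 degrees. Section 15-1 (3) applies the same one-sided two-sample t-test to DASH and to pain on the VAS.

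Section 15-3 (1) lists the methods: "Methods: One side, Two sample student t-test, Chi-square test" and Fisher's exact test. No regression, ANCOVA, mixed model or stratified test is named.

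The information that could be used is in the data plan. Section 11-1 (5) schedules "Physical function (Before surgery, after surgery 3, 6, 12 months", and section 11-1 (4) records "Operation date, Name of surgery, histopathological diagnosis, TNM stage, postoperative therapy". Section 6-2 says that pectoralis tightness and loss of shoulder motion among "patients who underwent the mastectomy are higher than those of patients who underwent the breast preservation surgery". Section 10.3 (2) adds that, to compare motion in patients "who underwent the partial mastectomy or total mastectomy, the subjects are assigned to each group randomly in similar proportion".

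**The concern.** The planned test uses baseline only by subtraction, which is the best use of it only if follow-up rises one for one with baseline. It makes no use of surgery type, which the protocol itself describes as prognostic and mentions when it describes allocation.

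The decision rests on a lower confidence limit measured against a fixed 10-degree margin. Every unnecessary tenth of a degree in the half-width therefore has to be made up by the observed difference. A change-score comparison also carries part of any chance baseline imbalance into the estimate when the slope is not 1.

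The method is written into the protocol, for primary and secondary endpoints alike. A later analysis plan that used ANCOVA would depart from the protocol, so the point belongs here.

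**Working it through.** **Inputs from the protocol (section 8-3).** One-sided alpha 0.025, power 90%, SD 10, 1:1 allocation, 86 evaluable per arm. The 86/86 rows have a true difference 5 degrees beyond the margin (10 against 5, or 15 against 10).

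**The plan's own figure.** A two-sample t-test with 86 per arm, SD 10 and distance 5 has noncentral-t power 0.9032, which matches the row printed as 0.90323; 85 per arm gives 0.8999. Allowing for dropout, 86/0.90 = 95.6, so 96 per arm. The sample size reproduces for the t-test.

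**Inputs the protocol does not give.** The baseline to follow-up correlation r, the baseline SD s0, the follow-up SD s1, the share of patients having mastectomy, and the size of its effect. These are assumed below.

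**Baseline adjustment (per-patient variances, large samples).**
- Change score: s0² + s1² − 2·r·s0·s1
- ANCOVA: s1²·(1 − r²)
- Difference: s0² − 2·r·s0·s1 + r²·s1² = (s0 − r·s1)²

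The difference is never negative. It is zero only when r·s1/s0 = 1, that is, when the slope of follow-up on baseline is 1. With k = s0/s1, the ratio of ANCOVA to change-score variance is (1 − r²)/(1 + k² − 2rk). For k = 1 this is (1 + r)/2.

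The half-width of the planned interval, taking SD 10 as the SD of change, is 1.974 × 10 × √(2/86) = 1.974 × 1.525 = 3.01 degrees. Multiplying by the square root of the variance ratio gives the ANCOVA half-width. The equivalent size is 86 divided by the ratio.

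| k | r | variance ratio | SE smaller by | equivalent t-test size per arm | half-width (degrees) |
|---|---|---|---|---|---|
| 1 | 0.3 | 0.65 | 19% | 132 | 2.43 |
| 1 | 0.5 | 0.75 | 13% | 115 | 2.61 |
| 1 | 0.7 | 0.85 | 8% | 101 | 2.78 |
| 0.5 | 0.3 | 0.91/0.95 = 0.96 | 2% | 90 | 2.95 |
| 0.5 | 0.5 | 0.75/0.75 = 1.00 | 0% | 86 | 3.01 |
| 0.5 | 0.7 | 0.51/0.55 = 0.93 | 4% | 93 | 2.90 |

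On the same reading of SD 10, power at 86 per arm rises from 0.903 to 0.981, 0.964 and 0.943 in the three k = 1 rows. With k = 1 and r = 0.9 the ratio is 0.95 and power is 0.917.

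**Surgery type.** If a share p of patients has mastectomy and these lose g degrees more, the proportion of variance explained is p(1 − p)g²/SD². With p = 0.5 and SD 10:
- g = 2: 0.25 × 4/100 = 0.01, power about 0.906
- g = 5: 0.25 × 25/100 = 0.0625, power about 0.92

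This is a small gain unless the effect of surgery type is large.

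**Cost in degrees of freedom.** Two extra covariates among 172 patients reduce the residual degrees of freedom from 170 to 168, which is negligible.

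**The case against.** **Validity is intact.** The t-test on change is unbiased under randomisation, the sample size was computed for it, and any loss of precision works against a superiority claim. This stands in full. A reader might infer that the primary result would be biased or wrong; the documents do not support that.

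**The gain is not guaranteed.** A reader might infer that the change score loses precision at every correlation below 1. That is true only if the baseline and follow-up SDs are equal, which the protocol does not say. Exclusion criterion (5) removes patients with a prior shoulder movement disorder, which could narrow the baseline spread, and surgery and radiotherapy could then widen it. In the k = 0.5 rows the gain is 0 to 4%. This objection stands, and it limits how large the gain can be said to be. It does not make ANCOVA the worse choice.

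**Surgery type may not be a stratification factor.** A reader might infer that the planned standard error is too large because allocation was stratified on surgery. Section 10.3 (2) describes block randomisation and defines no strata, and its sentence on similar proportions is ambiguous. The claim therefore holds only if allocation is in fact balanced on surgery type.

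**The outcome scale is loosely worded.** Section 8-3 states the hypothesis in group mean ROM without mentioning change. If follow-up values alone were compared, the ANCOVA variance ratio would be 1 − r² (0.91, 0.75 and 0.51 for r = 0.3, 0.5 and 0.7), so the advice is the same.

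**Baseline may be missing for some.** Section 15-3 foresees absence at Visit 1, so baseline is scheduled for every patient rather than known for every patient. A change score needs the same value, so ANCOVA loses no further patients.

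**The assumed difference equals the margin in one place.** Section 8-3 tests against 10 degrees and also lists 10 as the difference. At that value power equals alpha under any method. That is a separate matter, and precision counts for any true difference above the margin.

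**Conclusion.** The point holds as a matter of efficiency. The protocol fixes an unadjusted t-test on change while collecting two pieces of information that could sharpen it. In large samples ANCOVA on baseline is at least as precise, and it is strictly more precise unless the slope of follow-up on baseline is exactly 1.

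The size rests on assumptions. Over r = 0.3 to 0.7, the standard error falls by 8% to 19% if the two SDs are equal, and by 0 to 4% if the baseline SD is half the follow-up SD. Surgery type adds an amount that depends on its effect. If allocation is balanced on it, leaving it out makes the standard error somewhat too large.

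A reader might also infer that the trial is underpowered. Section 8-3 does not say whether the SD of 10 is of change or of a single measurement. Only on the second reading, with equal SDs and r = 0.3, does the planned test fall to power 0.787 (0.928 for ANCOVA); on the first it keeps 0.903. The documents do not establish a shortfall. The change is worth making because it costs almost nothing.

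**What to change.** In 15-1 (2), 15-1 (3) and the method list in 15-3, replace the two-sample t-test for the efficacy endpoints with ANCOVA at each visit. The terms are arm, the baseline value of the same measure, and surgery type (mastectomy or breast preservation). In 15-1 (2), apply the lower-confidence-limit rule to the adjusted arm difference. Keep the t-test on change as a sensitivity analysis.

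The cost is a sentence or so in each place. No visit, measurement or patient is added, and the sample size can stay as it is. The covariates should be fixed before unblinding so that their choice cannot appear to depend on the results.

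### The planning difference of 10 degrees equals the null boundary, so the stated success rule has 2.5% power at that difference, not 90%

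*Protocol*

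**What the plan says.** Section 8-3 of the protocol writes the hypotheses as H0: D ≤ 10 against H1: D > 10, where D is the experimental-group mean range of motion minus the control-group mean. Its numbered assumptions include:

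- "Significance level α = 0.025"
- "Type 2 error (β) is 0.1, and statistical power 90% is maintained"
- "The difference in the average value between two groups: 10 degree" (assumption 4)

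The text above the hypotheses gives an SD of 10 and 96 subjects per group after 10% dropout. The power table lists 86 per group at SD 10 and about 90% power twice: once with margin 5 and actual difference 10 (printed power 0.90004), and once with margin 10 and actual difference 15 (printed power 0.90323). The text does not say which row was used.

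Section 15-1 (2) analyses the primary endpoint by "performing the one side and two sample student T-test with the difference and the variance between two groups measured at each period". It then concludes that "the investigational group is superior to the control" when the difference exceeds 10 degrees, explained as "that is the lowest value of confidential interval is over 10".

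**The concern.** The figure of 10 degrees serves as three things at once: the clinically relevant difference, the boundary of the null hypothesis, and the effect assumed for planning. The first two can coincide, but the last two cannot. A test of D ≤ 10 has rejection probability equal to its significance level when D is exactly 10, whatever the sample size.

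A reader of 8-3 would believe that the trial has a 90% chance of success if the device improves motion by 10 degrees. Under the success rule as written, that chance is about 1 in 40. A device that delivered exactly the planned benefit would almost certainly be reported as not superior.

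**Working it through.** **Inputs.** From 8-3: one-sided α = 0.025, SD = 10, 1:1 allocation, 86 evaluable per group, 10% dropout, H0: D ≤ 10, assumed difference 10. From 15-1: success if the lower confidence limit is above 10. Section 15-1 gives no confidence level; I take the two-sided 95% interval, which matches one-sided 0.025.

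**Step 1: reproduce the 86.** What matters is the gap between the actual difference and the margin, which is 5 degrees in both rows (10 − 5 and 15 − 10).

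- Normal approximation: n = 2 × (1.960 + 1.282)² × 10² / 5² = 84.1, so 85 per group.
- Noncentral t: power is 0.8999 at 85 and 0.9032 at 86, so 86 per group.
- Dropout: 86 / 0.9 = 95.6, so 96 per group and 192 in total.

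The plan's figures are reproduced. The 0.9032 agrees with the 0.90323 printed for margin 10 and difference 15. An ordinary test against zero with a difference of 10 would need only 2 × (1.960 + 1.282)² × 10² / 10² = 21.0, so 22 per group. The 86 therefore comes from a null shifted away from zero.

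**Step 2: the observed difference that the rule requires.**

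- SE = 10 × √(2/86) = 1.525 degrees.
- t(0.975, 170 df) × SE = 3.01 degrees.
- The lower limit exceeds 10 only if the observed difference exceeds 10 + 3.01 = 13.01 degrees.

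**Step 3: power at 86 per group and SD 10.**

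| Margin tested | True difference | Observed difference needed | Power |
|---|---|---|---|
| 10 (H0 and 15-1) | 10 (assumption 4) | 13.01 | 0.025 |
| 10 (H0 and 15-1) | 13 | 13.01 | 0.499 |
| 10 (H0 and 15-1) | 15 | 13.01 | 0.903 |
| 5 | 10 (assumption 4) | 8.01 | 0.903 |

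**Step 4: does more data help?** With all 96 per group evaluable, SE = 10 × √(2/96) = 1.443 and the required observed difference falls to 12.85. Power at a true difference of 10 is still 0.025; at 15 it is 0.931.

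**Step 5: set the statements against the two table rows.** Margin 10 with difference 15 agrees with H0 and 15-1 but contradicts assumption 4. Margin 5 with difference 10 agrees with assumption 4 but contradicts H0 and 15-1. No row of the table has margin 10 and difference 10.

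**The case against.** The best defence is that the sample size is sound. The table contains a row that matches H0 and the 15-1 rule and gives 86 per group at 90% power, so assumption 4 may be a loose statement of the margin. The arithmetic part stands: 86 is correct for a 5-degree gap. But assumption 4 is listed as the difference between the group averages, the text of 8-3 derives the sample size from a 10-degree difference, and 15 degrees appears only as a table entry. The stated power is therefore attached to the wrong effect. Since the protocol itself fixes these values, this is not a matter left to a statistical analysis plan.

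A reader might go further and infer two competing success thresholds. Section 15-3 lists "Methods: One side, Two sample student t-test" without a null value, and 15-1 uses the same test for DASH and pain, which have no margin. Read as a test against zero, the primary t-test would be significant from an observed 3.01 degrees, while the interval rule needs 13.01. The documents do not support this. No section sets the primary null at zero; 8-3 sets it at D ≤ 10, and 15-1 ties superiority only to the lower limit. A one-sided 0.025 t-test of D ≤ 10 and a two-sided 95% lower limit above 10 are the same test: they agreed in all 10,000 simulated trials. There is one threshold, at about 13 degrees. What remains is that 15-1 does not restate the null or the confidence level, a small clarity gap that a cross-reference closes.

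**Conclusion.** The point holds as a contradiction between the hypotheses, the planning difference and the stated power. At the assumed difference of 10 degrees, the success rule of 15-1 has 2.5% power against the 90% claimed. The 90% applies to a true difference of 15 degrees under the stated null, or to a 5-degree margin that the hypotheses and 15-1 do not use.

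The 13.0-degree threshold and the 90% figures assume SD 10, 86 evaluable per group and a two-sided 95% interval. The 2.5% depends only on the one-sided level of 0.025 and on the assumed effect lying on the null boundary; it does not change with SD or sample size. The protocol must be corrected because a stated operating characteristic is wrong, but the documents do not show two rival definitions of success.

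**What to change.** Reconcile the margin and the assumed difference across 8-3 and 15-1, and name the table row on which the sample size rests.

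- **If H0: D ≤ 10 and the 15-1 rule are kept:** restate assumption 4 as a true difference of 15 degrees, say that 86 per group then gives about 90% power, and say that power at a true difference of 10 is 2.5%. The cost is a less favourable assumption that the sponsor must justify. No extra patients are needed.
- **If the planning difference of 10 is kept with the margin-5 row:** the hypotheses in 8-3 and the 10-degree limit in 15-1 would both have to change, and the margin would need its own justification, because 8-3 and 15-1 now rest on 10 degrees. The 86 per group would again stand.

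For clarity, add to 15-1 (2) that the primary t-test is of H0: D ≤ 10 at one-sided 0.025, equivalent to the lower limit of the two-sided 95% interval exceeding 10. In the same edit, align 15-3, which gives "Statistical power: 80" per cent, with the 90% in 8-3. All of this is protocol wording.
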